### **3.8 Justification of the choice of the investigation population**

The Glucosafe 2 software has been developed to meet the specific needs of critically ill ICU patients. The pre-clinical and clinical studies performed with its predecessor, Glucosafe, also have been made in this population to evaluate its predictive accuracy. The population of critically ill patients is characterized by a severe catabolic state due to a generalized inflammation, with high insulin resistance and increased proteolysis. In the acute phase, the patients' endogenous reserves (glucose, amino acids and fatty acids) are massively mobilized, and not taking account of this process may lead to overfeeding during this acute phase. Glucosafe 2 takes into account the entire metabolism of intensive care patients in every phase and accordingly provides advice on both blood glucose management and nutritional therapy [9, 13]. All of these are reasons why Glucosafe 2 should be tested specifically in intensive care patients and cannot be extended to other "general patient populations" that do not have these prerequisites.

## **4. CLINICAL INVESTIGATION OBJECTIVES**

### **4.1 Overall Objective**

The purpose of this study is to evaluate the performance and the security of GS2 software in comparison to the actual clinical practice (according to local protocols). The aim is to improve nutrition management and BG control during the ICU stay.

### **4.2 Primary Objective**

The primary objective of the experimental study is to assess whether GS2 improves the blood glucose control and monitoring, which is reflected in an increased time on target (glycaemia between 5.0 and 8.5 mmol/l) compared to standard care.

### **4.3 Secondary Objectives**

The secondary objectives are to assess whether GS2 stabilizes BG and reduces the variability in BG measurements and improves nutritional management by increasing the achievement of the daily energy and protein target by limiting the cumulated energy and protein debt compared to the standard of care.

### **4.4 Safety Objectives**

The study will assess the safety of GS2 by decreasing the hypoglycaemic and hyperglycaemic episodes in comparison to the standard of care.

## 5. CLINICAL INVESTIGATION OUTCOMES

### 5.1 Primary Outcome

Time-in-target (range: 5.0 to 8.5 mmol/l) per patient and in the cohort.

For the purpose of calculating time-in target, BG values are considered constant from one measurement to the next. The time-in-target is defined as the cumulative time in the 5 to 8.5 mmol/l range divided by the time from the first BG measurement to 2 hours after the last BG measurement.

### 5.2 Secondary Outcomes

Glycaemic “variability”:

- Mean and SD of BG measurements per day and per patient during the enrolment period
- Maximum of daily BG difference

Achievement of nutritional targets.

- Estimates of energy expenditure, protein requirements, caloric target and protein target are made on a daily basis in the intervention and control groups, as detailed in sect. 8.1.1 and 8.1.2, respectively.
- The caloric target for the day is reached when of 80-100% of the target is achieved.
- The protein target for the day is reached when of 80-100% of the target is achieved.
- Cumulated energy debt, defined as daily energy expenditure minus caloric intake, cumulated over the enrolment period.
- Cumulated protein debt, defined as daily protein requirement minus protein intake, cumulated over the enrolment period.

Prediction of blood glucose (BG)

- Root mean squared prediction error as a measure of the differences between BG predicted by GS2's metabolic model and measured BG. The prediction error will be calculated, as a function of time elapsed since last BG measurement, per patient, per cohort (sect. 9.2.3).

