### 5.3 Other Outcomes of Interest

Workload:

- Frequency of daily and cumulated BG measurements per patient and in the cohort during the patient's enrolment period (duration of the ICU stay with a max of 15 days).
- Frequency of daily and cumulated adjustments of insulin and nutrition pump settings during the patient's enrolment period.

Compliance (only in intervention arm)

- Number of episodes per patient and in the cohort where a BG measurement is not followed up within 30 minutes by an accepted GS2 advice (during the enrolment period)
- Number of episodes per patient and in the cohort where GS2 advice was accepted by the nurse but pumps were not set according to the advice within 30 min by the nurse (nurse did not notice, was too busy, forgot, or misinterpreted advice = true errors)
- Number of advices given by GS2 which were accepted, accepted with modification or rejected

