## Calculation of due time for the next blood glucose measurement

GS2 uses the BG prediction error to calculate the maximum time until the next BG measurement is due. The purpose of this is to keep the hypoglycaemia risk at any time below the acceptable risk maximum of 0.05% per measurement, or 2% per patient (under the assumption that one patient has on average about 40 measurements taken, 2% is given by  $0.05\% \times 40$ ). The prediction error is a function of the prediction time, the longer the prediction, the larger is the "uncertainty" of the predicted BG, and thus the "uncertainty curve" has the shape of a "funnel", as can be seen in Fig. 7 above (light-pink shaded area beneath the thicker black line depicting the predicted BG in the upper left-hand plot).

A close-up of Fig. 7 with annotations in text is shown below. The time of the next measurement is when 1) the first time the lower edge of the uncertainty curve reaches the hypoglycaemia threshold, or 2) the next measurement is due according to local department rules, when that is sooner than 1).

[figure not shown]

A close-up of Fig.7 upper left-hand panel: The next BG measurement is due at 20:08, when the lower edge of the uncertainty area (light-pink shaded) the first time touches the hypoglycaemia threshold (dashed horizontal line) after the most recent BG measurement (red squares). The BG target range is depicted as light-green area, and each BG measurement shows the insulin sensitivity that was calculated at the time of the measurement.

In mathematical terms, the "uncertainty curve" at each time  $t$  for the predicted BG concentration is:

$$UC(t) = \exp(\ln \text{predicted BG}(t) + \text{Norm.Inv}(0.0005) * \ln PE(t))$$

where 0.0005 or 0.05% is the "Hypoglycaemia Risk Maximum" setting, i.e., the highest risk of hypoglycaemia deemed acceptable.  $\text{Norm.Inv}(0.0005) = -3.29$  is the inverse of the cumulative normal distribution.

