### 8.1.2 Control Intervention (standard/routine/comparator)

The current local protocols for glycaemia control and nutrition management will be used in the control group and in the historical control group for comparison.

After ICU admission, a BG measurement is performed. If glycaemia is in the accepted range (5.0-8.5 mmol/l) or spontaneously normal (4.0 to 5.5 mmol/l), no correction is proposed. In this case, a BG control should be done every 2 hours. In case BG measurements are twice  $> 8.5$  mmol/l, a new control is proposed in another sampling site. If the BG measurement is still  $> 8.5$  mmol/l, an IV insulin-therapy should be initiated following the local protocol. A further BG control should be done within the next 15-30 minutes until stability of the BG. Then, BG controls should be done every 2 hours. If BG measurement are  $< 4$  mmol/l, insulin-therapy should be stopped (if in progress) and a correction can be performed. A new control is done within 15 minutes. If the glycaemia is still under 4, a new correction is done. If the glycaemia is spent above 4, BG control are spaced to every 30 minutes. Then, when the glycaemia spent above 5, BG control are done every 2 hours. The algorithm of the local glycaemia control ICU protocol is presented in Figure 9.

[figure not shown]

Figure 9. Algorithm of the local glycaemia control ICU protocol (control and historical control group)

An estimation of caloric target is performed after the admission in the ICU. Then, if the patient stays more than 4 days and if the indirect calorimetry measurement is achievable, the measurement is performed, and the caloric target is adjusted. If gastro-intestinal tract is functional and there are no contraindications to enteral nutrition, it is started from day 1 with an appropriate solution regarding the pathologies and with an initial debit of 25 ml/h or 10 ml/h for a patient with severe shock (can be adapted according to tolerance). The 80-100% of the energy target need to be achieved at the end of day 3. If the energy target (80-100%) is not covered at day 4, a SPN (Supplemental Parenteral Nutrition) is indicated to cover the target.

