### 9.2.2 Assessment of secondary outcomes

Glycaemic “variability”:

Mean and SD of BG

- All BG measurement will be reported in the eCRF daily. The mean BG with SD will be calculated from those data.
- Maximum of daily BG difference

Achievement of nutritional targets.

The protein goal is met (e.g., 80-100% of the accumulated target)

- In the control group, the total intake of protein per day is going to be reported in the eCRF. Then, it is going to be compared with the daily target and the percentage will be made. The mean percentage for the duration of the study will then be calculated.
- In the intervention group, the comparison between the daily intake and the daily target is carried out automatically by GS2. The percentage will be reported directly in the eCRF. The mean percentage for the duration of the study will when be calculated.

The caloric goal is met (e.g., 80-100% of the accumulated target)

- In the control group, the total intake of energy per day is going to be report in the eCRF. Then, it is going to be compared with the daily target and the percentage will be made. The mean percentage for the duration of the study will when be calculated.
- In the intervention group, the comparison between the daily intake and the daily target will be made automatically by GS2. The percentage will be directly report in the eCRF. The mean percentage for the duration of the study will then be calculated.

Energy debt at the end of the stay

- In the control group, the total intake of energy per day is going to be reported in the eCRF. The daily energy target will be reported every day as well. Then the total energy debt is calculated as the addition of the daily difference between the energy target and the energy intake.
- In the intervention group, the energy debt will be directly calculated and extracted from GS2.

Protein debt at the end of the stay.

- In the control group, the total intake of protein per day is going to be reported in the eCRF. The daily protein target will be reported every day as well. Then, the total protein debt will be calculated as the addition of the daily difference between the protein target and the protein intake.
- In the intervention group, the protein debt will be directly calculated and extracted from GS2.

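### Mean BG and SD are calculated from unweighted readings although reading times depend on glucose and differ by arm, so raw mean BG can look lower under GS2 when true glucose is identical

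*Protocol*

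**What the plan says.** Section 5.2 of the protocol lists two variability outcomes: "Mean and SD of BG measurements per day and per patient during the enrolment period" and "Maximum of daily BG difference". Section 9.2.2 has every BG value entered in the eCRF and adds: "The mean BG with SD will be calculated from those data". Neither section weights by time, sets a common time grid or adjusts for the number of readings.

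Reading times are set differently in the two randomised arms.
- **Standard care (8.1.2).** Readings are 2-hourly in range. After insulin is started for repeated values above 8.5 mmol/l: "A further BG control should be done within the next 15-30 minutes until stability of the BG". Below 4 mmol/l the recheck is at 15 minutes, then half-hourly until glucose passes 5.
- **GS2 (8.1.1, on due times).** "GS2 uses the BG prediction error to calculate the maximum time until the next BG measurement is due". The next reading falls at the earlier of two times: "the first time the lower edge of the uncertainty curve reaches the hypoglycaemia threshold", or "the next measurement is due according to local department rules, when that is sooner than 1".

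Reading frequency is itself an outcome in 5.3: "Frequency of daily and cumulated BG measurements per patient and in the cohort during the patient's enrolment period". By contrast, time in target (5.1) and time in hyperglycaemia (9.2.4) hold each value until the next reading, so they are time-weighted.

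**The concern.** An unweighted mean of readings estimates mean glucose only if the reading times are unrelated to the glucose level. Here they are related, and in different ways. Standard care reads densely after high values, and also around low ones. GS2 reads sooner the lower the predicted glucose. With the same glucose in both arms, the raw means need not agree. The mixed-effects models of 11.4.3 do not remove this, because the dependence lies in when the outcome is observed.

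The maximum daily difference is a sample range, and a sample range grows with the number of readings.

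At stake is the secondary objective in 4.3 that GS2 stabilises glucose and reduces variability. Part of a difference in mean BG could come from the measurement schedule.

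**Working it through.** **The plan's own figure.** The protocol gives no figure for mean BG, SD or daily range. Its group size (11.2: difference 10 points, SD 21, 80% power, two-sided 5%) is used below only for a standard error. The normal formula 2 × (1.96 + 0.84)² × 21² / 10² gives about 69.2, so 70. The t-based value is 70.2, so 71. Power at 71 is 81.0%. The stated 71 is reproduced.

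**Step 1: how GS2 due times depend on glucose.** From the curve in 8.1.1, the lower edge is BG × exp(−3.29 × PE(t)), with PE read as the log-scale error of 9.2.3. Setting this equal to a threshold T gives BG = T × exp(3.29 × PE). The GS2 threshold is not in the text; T = 3.2 mmol/l is assumed (the mild hypoglycaemia limit of 5.4). The prediction errors come from 3.3.2.

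| Horizon | PE, lower to upper | BG at which the reading falls due |
|---|---|---|
| 1 h | 10% to 17% | 4.45 to 5.60 |
| 2 h | 17% to 26% | 5.60 to 7.53 |
| 3 h | 21% to 29% | 6.39 to 8.31 |

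Example: 3.2 × exp(3.29 × 0.26) = 7.53. At the upper error, any value below about 7.5 mmol/l brings the next reading forward of 2 hours.

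**Step 2: identical glucose, two schedules.** 1,500 simulated glucose paths were each read once under the control rule and once under the GS2 rule, so the true difference is zero. Assumptions:
- log-scale mean-reverting paths starting at 10.5 and settling near 7.2 mmol/l, 3 to 10 days long (true mean 7.52, true SD 1.49, time in target 68% as in 11.2);
- control rechecks every 30 minutes after two values above 8.5 until the change is under 0.5 mmol/l, and the low-glucose rechecks of 8.1.2;
- PE interpolated linearly from 5% at time zero.

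Control gave a raw mean of 7.71, raw SD 1.62, maximum daily difference 4.06 and 14.3 readings per day. GS2 minus control (mmol/l):

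| GS2 scenario | Readings/day | Raw mean | Raw SD | Raw max daily difference | Time-weighted mean | Time-weighted SD |
|---|---|---|---|---|---|---|
| Local rechecks also run, upper PE | 18.3 | −0.30 | +0.01 | +0.12 | +0.03 | −0.02 |
| Local rechecks also run, lower PE | 14.9 | −0.06 | +0.01 | +0.01 | +0.01 | −0.01 |
| 2-h cap only, upper PE | 16.5 | −0.52 | −0.07 | +0.03 | +0.05 | 0.00 |
| 2-h cap only, lower PE | 12.9 | −0.27 | −0.07 | −0.08 | +0.03 | +0.01 |
| 4-h cap, lower PE | 8.1 | −0.45 | −0.06 | −0.60 | +0.10 | 0.00 |
| 2-h cap, upper PE, threshold 4 | 28.1 | −0.83 | −0.17 | +0.20 | +0.07 | +0.02 |

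Both arms can contribute. In the 2-h cap, upper PE row, control is 7.71 − 7.52 = +0.19 above the truth and GS2 is 7.19 − 7.52 = −0.33 below it; −0.33 − 0.19 = −0.52.

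**Step 3: chance of a spurious p < 0.05 for raw mean BG at 71 per arm.** With local rechecks and the upper PE, the simulated between-patient SDs are 1.24 and 1.14, pooled 1.19. The standard error is 1.19 × √(2/71) = 0.20, so z = 0.303/0.20 = 1.52 and the chance is 33%. With the lower PE it is 6%. With the 2-h cap only it is 78% (upper PE) or 32% (lower PE).

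**Step 4: averaging by day.** Section 5.2 can also be read as daily means, which weight days equally. Further runs with identical glucose, with local rechecks under GS2, gave −0.10 to −0.35 pooled and −0.04 to −0.17 as a mean of daily means, about half. Halving −0.303 gives z of about 0.76 and a chance of about 12%, if the standard error is unchanged.

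**Step 5: a common 2-hour grid for the daily difference.** The arm difference is then −0.04 to +0.05, except −0.46 with 4-h GS2 intervals. A grid cannot restore readings that were never taken.

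**The case against.** The strongest reply is that the GS2 timing rule has two parts. If the local rechecks also govern GS2 patients whenever they fall sooner, much of the contrast between the schedules goes. This stands: it cuts the bias in mean BG to roughly 0.04 to 0.35 mmol/l, and the SD bias is then near nil (+0.01 to +0.02). It does not remove the bias, because GS2 still adds readings when predicted glucose is low.

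Several stronger conclusions are tempting and not supported.
- **That the bias is 0.4 mmol/l or more as a matter of course.** This needs GS2 to skip the local rechecks. Larger values still would need control rechecks to continue until glucose is back in range, whereas 8.1.2 says until stable.
- **That GS2 will look less variable.** The SD favours GS2 only modestly (−0.06 to −0.17), and only when the local rechecks do not run there.
- **That the daily difference favours GS2.** A reader might take the predecessor trial in 3.3.3 (study d) as a guide: 170/0.76/24 = 9.3 readings per patient-day with the device and 171/0.51/24 = 14.0 in control. That assumes four full days for each of 12 patients, and 3.3 disclaims equivalence with GS2. Section 5.3 lists reading frequency without predicting a direction. Section 6.1 expects fewer readings only if prediction error is smaller, and 3.4 expects more if it is larger.
- **That the 7.0 against 8.0 mmol/l in that trial was a sampling artefact.** Nothing in the protocol shows this.

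An analysis plan, not at hand, could add weighting. The protocol nonetheless already states a calculation from unweighted readings, next to two outcomes that it does time-weight.

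**Conclusion.** The concern holds for mean BG. In every simulated scenario with identical glucose the raw mean was lower under GS2: by roughly 0.04 to 0.35 mmol/l if the local rechecks also run under GS2, and by up to about 0.4 to 0.8 if they do not. It is about half as large when daily means are averaged. Time-weighting leaves +0.01 to +0.10. The direction for mean BG is well supported; the size is not fixed, because it rests on an assumed glucose process, an assumed GS2 threshold, and a reading of the local rule without Figure 9.

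For SD the bias is near nil to modestly in GS2's favour. For the maximum daily difference it can go either way (−0.60 to +0.20 in the scenarios above).

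These are secondary outcomes. The superiority conclusion in 11.4.2 rests on time in target, which is time-weighted, so that outcome's definition and the 71 per group are untouched.

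**What to change.** In 5.2 and 9.2.2, define mean BG and SD as time-weighted values, holding each reading until the next, as 5.1 and 9.2.4 already do. Report the raw-reading mean and SD descriptively. Holding values constant is preferable to interpolating: it keeps one convention throughout, and interpolation smooths the less often read arm more (in simulation the interpolated SD was 0.98, 0.96 and 0.92 of the true SD at 1-, 2- and 4-hour spacing).

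Keep the maximum daily difference as descriptive, reported beside the number of readings per day. Add a sensitivity analysis on a common time grid, stating that a grid cannot correct for longer reading intervals in one arm.

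The cost is wording and minor programming. Values and times are already in the eCRF (9.2.1), and no patient procedure changes. The downside is slightly less direct comparability with earlier reports based on raw readings.

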| Intervention:                         | 
Intervention group: number of patients: 71.
 
Glucosafe 2 software is used for 15 days or until the patient is discharged from the ICU or starts eating (oral feeding). Glucosafe 2 integrates the following data: body weight (BW), age, gender, type of diabetes, renal replacement therapy, serial blood glucose measurements, insulin therapy and the nutrition support (including non-nutritional calories). Based on those data and according to the mathematical model it contains, Glucosafe 2 will calculate patients' insulin sensitivity and will recommend the dose of insulin and nutrition required for each ICU patient. For more information, see point 8.1.1.
                                                                                                                                                                                                                                                |
| Control intervention (if applicable): | 
Control group: number of patients: 71.
 
Standard care according to department (ICU-HUG) protocol. BG measurement will be made every 2 hours for all patients admitted in the ICU. Depending on the stability of those measurements, BG control will be made in a close or extended way according to our internal protocol.
 
Early enteral nutrition will be started within 48 hours if the medical situation allows it. Nutrition will be given in a progressive way with the aim of covering the energy and protein needs at the end of day 3. For more information, see point 8.1.2.
 
Historical control group: number of patients: 71.
 
Retrospective data, with standard care before the beginning of the pilot study. Historical controls data will be retrospectively collected from the patients' computerized record. They will be recruited within 2 years before the trial starts.
 |

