Nutritional targets are set once every day by the attending physician. To set the nutritional targets the user must provide an estimate of the patient's Current Energy Expenditure (EE) and of the patient's Acuteness factor. The estimated EE is provided by clicking on one of the three "apply" buttons for Indirect Calorimetry, Free estimate or 25 kcal/kg/day. In the example in Figure 6. Indirect Calorimetry has been selected, resulting in an estimate of 2160 kcal/d for EE. The patient's Acuteness factor is provided by typing it (70%) in the Acuteness factor field and clicking "apply". The Acuteness factor is by default set to 20% at admission to the ICU and is automatically increased by 10% at the beginning of each nurse shift, until it reaches 100%. It can be set to any value between 0% and 100% at any time. The Caloric target is then calculated as the product of EE and the Acuteness factor (1512 kcal/d). The Proteins required (124 g/d) are calculated as the Daily requirement (1,3 g/kg/d) multiplied by the patient's weight (or ideal weight, if the BMI is above 25kg/m²). The Protein target (86 g) is then calculated as the Protein Target multiplied by the Acuteness factor. The Final Protein Target (112 g/d) is the same as the Protein Target, unless the patient is on hemofiltration, in which case it is 130% of the Protein Target.

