If enteral nutrition is contraindicated, a parenteral nutrition can be initiated in a progressive way. It can be either by a central venous access or by a peripheral one. Vitamins and trace elements should be supplemented with 1 ampoule of Addaven® and 1 ampoule of Cernevit®. Glutamine supplements can also be added on a case-by-case basis. If tolerance is good, PN is progressively increased to achieve 80-100% of the energy target by the end of day 3. The algorithm of the local ICU nutrition management protocol is presented in Figure 10.

[figure not shown]

*Figure 10. Algorithm of the local ICU nutrition management protocol (control and historical control group)*

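### Section 5.2 promises daily energy and protein estimates in both arms, but the text of 8.1.2 does not describe them for control, so nutrition outcomes can differ by method and not by feeding

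*Protocol*

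**What the plan says.** **Section 5.2 (Secondary Outcomes)** states: "Estimates of energy expenditure, protein requirements, caloric target and protein target are made on a daily basis in the intervention and control groups". It points to 8.1.1 for the intervention arm and 8.1.2 for control. It defines energy debt as daily expenditure minus intake and protein debt as daily requirement minus intake, each summed over enrolment. A day's target counts as reached at 80-100%.

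**Section 8.1.2 (control)** states: "An estimation of caloric target is performed after the admission in the ICU". The target then changes by one route: "if the patient stays more than 4 days and if the indirect calorimetry measurement is achievable, the measurement is performed", after which the caloric target is adjusted. The text goes on to feeding routes and to reaching 80-100% of the energy target by the end of day 3. It gives no protein requirement or protein target. It adds: "The algorithm of the local ICU nutrition management protocol is presented in Figure 10". That figure is not visible in the text reviewed.

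**Section 8.1.1, Setting the nutritional targets (GS2 arm)** states: "Nutritional targets are set once every day by the attending physician". The user chooses calorimetry, a free estimate or a per-kilogram value for energy expenditure, with no condition on length of stay. The protein rule is explicit.

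**Section 9.2.2** has control energy and protein targets recorded daily in the eCRF, for protein in the words "The daily protein target will be reported every day as well". It computes control debts as target minus intake. For the GS2 arm, debts and percentages come directly from the software.

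**The synopsis** lists energy expenditure, by calorimetry or a formula, and both targets among the daily data, where routine measurement allows. It describes control nutrition as given "with the aim of covering the energy and protein needs at the end of day 3".

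**The concern.** Percent of target divides intake by a reference, and cumulated debt subtracts intake from one. If the reference is derived by different rules in the two arms, part of any difference between arms comes from the reference. If its source switches partway through a control patient's stay, achievement and debt can move with no change in feeding. In control, only patients who stay beyond 4 days and can be measured contribute calorimetry-based days, so the measured part of the data is also a selected part.

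Nutritional achievement is a named secondary objective, and Section 11.4.3 plans mixed-effects models for the repeated daily goals. A reader of the results would take a difference in achievement or debt as a difference in nutrition delivered.

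**Working it through.** The plan states no figure for the size of this effect, so the check compares the sections and then illustrates what a change of reference can do.

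**1. The sections side by side**

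| | GS2 arm (8.1.1, 9.2.2) | Control (8.1.2, 9.2.2) |
|---|---|---|
| Energy reference | renewed daily; calorimetry, free estimate or per-kg value | one estimate after admission; one conditional adjustment |
| Calorimetry | no day condition; the example patient has it applied at 45 h of ICU stay | only if stay exceeds 4 days and achievable |
| Protein requirement | 1.3 g/kg/d times weight | not in the text of 8.1.2; Figure 10 not visible |
| Debt | taken from the software | target minus intake |
| Debt as defined in 5.2 | expenditure or requirement minus intake | expenditure or requirement minus intake |

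Daily recording in 9.2.2 and in the synopsis gives a value for each control day. It does not say how that value is derived, and the synopsis allows calorimetry and formula values in the same series.

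**2. The protocol's worked GS2 example (text and Figure 6 of 8.1.1)**

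- Caloric target = expenditure × acuteness factor = 2160 × 0.70 = 1512 kcal/d, as stated.
- Protein required = 1.3 × 95 = 123.5, shown as 124 g/d. Times 0.70 this is 86 g/d, and times 1.30 for hemofiltration it is 112 g/d, as stated.
- Expenditure minus target = 2160 − 1512 = 648 kcal/d. Whether debt is taken from expenditure (5.2) or from target (9.2.2, control) therefore matters, and the visible text does not say which of the two the software uses.

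**3. Gap between methods in the same example**

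- Displayed per-kilogram value 2280 against calorimetry 2160: 2280 − 2160 = 120 kcal/d, and 120/2160 = 5.6%.
- The display does not equal 25 kcal/kg times either weight shown. 25 × 95 = 2375 gives a gap of 215 kcal/d (10.0%), and 25 × 88.2 = 2205 gives 45 kcal/d (2.1%).
- This is one illustrative screen and not trial data.

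**4. Effect on the 80-100% criterion, intake unchanged**

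New achievement = old achievement / (1 + c), where c is the relative change of target when calorimetry replaces the estimate. The ±10% and ±20% rows are assumptions.

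| c | from 80% | from 90% | from 100% |
|---|---|---|---|
| −20% | 100% | 112.5% | 125% |
| −10% | 88.9% | 100% | 111.1% |
| −5.3% (2280 to 2160) | 84.4% | 95.0% | 105.6% |
| +10% | 72.7% | 81.8% | 90.9% |
| +20% | 66.7% | 75.0% | 83.3% |

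Even the 5.3% step takes a day at 100% outside the band, while a day at 90% stays inside it.

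**5. How much control follow-up calorimetry could cover**

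Assume inclusion on ICU day 2 and measurement from ICU day 5. Coverage = days from day 5 on / follow-up days. Ending on ICU day 4: 0/3 = 0%. Day 5: 1/4 = 25%. Day 7: 3/6 = 50%. Day 10: 6/9 = 67%. Full 15 days: 12/15 = 80%. These are upper limits, because measurement must also be achievable. With the example gap, the largest shift in cumulated energy debt would be 12 × 120 = 1440 kcal.

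**The case against.** The best defence is that this is an incomplete cross-reference. Section 8.1.2 does not exclude daily review of the target, and both 9.2.2 and the synopsis provide for daily control values, which agrees with 5.2. In addition, 8.1.1 permits calorimetry but does not schedule it, and a GS2 patient whose source changes would show the same step. All of this is fair. It limits the claim to what can happen under the written rules and says nothing about how often. It does not remove the conflict, because recording a target daily does not make its derivation the same in the two arms.

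A reader might infer three stronger things that the documents do not support:

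- **That control protein outcomes have no basis or cannot be calculated.** The control protein target is recorded daily and 9.2.2 gives the formula. Figure 10 may hold the rule for setting it. Only the derivation is missing from the visible text.
- **That the planned models will mistake the step for an arm-by-time effect.** Section 11.4.3 names mixed-effects models but states no such term. Cumulated debt is one value per patient, and 9.2.2 averages percentages over the study.
- **That the shift is 10-20% of expenditure, or 216-432 kcal/d at 2160 kcal/d.** That range is assumed; the example as displayed shows 120 kcal/d.

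It can also be objected that replacing calorimetry with a formula discards better information. That stands against replacing it outright, but not against reporting a common-reference analysis alongside.

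**Conclusion.** The point holds in a limited form. Section 5.2 attributes to 8.1.2 daily control estimates that its text does not describe, and 5.2 and 9.2.2 define debt from different quantities. Followed as written, the rules let the reference for achievement and debt differ between arms and change within a control patient for reasons of method.

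The size and direction are unknown. They depend on how often calorimetry is done, when, and how far it departs from the estimate, none of which the protocol gives. The only internal indication is the single example, 120 kcal/d or 5.6%.

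The secondary nutrition outcomes are affected. The primary outcome rests on blood glucose alone, so it and the 71 per group are untouched. A separate SAP could settle the formula, but the conflict lies between sections of the protocol and should be corrected there.

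**What to change.** 1. Reconcile 5.2, 8.1.2, 9.2.2 and the synopsis. They should state how often each quantity is estimated in control, by what method, and where the control protein requirement comes from. If Figure 10 contains it, 5.2 should cite the figure.
2. Choose one definition of debt, from expenditure and requirement or from target, and use the same formula in both arms. State what the GS2 export contains so that it can be matched or recalculated.
3. For outcome calculation only, compute energy and protein achievement and debt in both arms against one common reference derived identically in each, for example weight-based from the baseline weight already collected. Report this alongside the analysis that uses the values in clinical use.
4. Report calorimetry use by day and arm.

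The cost is protocol wording and a recalculation from weight and intake data already collected. The common reference is less individual than calorimetry. It also answers a slightly different question from target achievement, because the GS2 caloric target is expenditure scaled by the acuteness factor; this is why both analyses should be shown. Bedside targets do not change.
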